## Abstract

**Introduction:**

People with intellectual disability (ID) are more likely to experience loneliness and have smaller social networks, which increases vulnerability to depression. Befriending may reduce depressive symptoms in other populations, but randomised controlled trials (RCTs) have not been carried out in this population. This pilot study aims to assess the acceptability and feasibility of carrying out a full RCT of one-to-one befriending by volunteers for people with ID, compared with an active control group.

**Methods and analysis:**

The trial aims to recruit 40 participants with ID. Participants in the intervention arm will receive weekly visits from a volunteer over 6 months. Community befriending schemes will recruit, train, supervise volunteers and match them to individuals with ID. Both groups will receive a booklet about local activities and have access to usual care. Health and social outcomes will be measured at the end of the intervention and 6 months’ follow-up. The following outcomes will be assessed: (1) recruitment and retention of individuals with ID and volunteers in the trial, (2) adverse events related to the intervention, (3) the acceptability of the intervention, (4) whether the intervention is delivered as intended, (5) changes in health and social outcomes and (6) the feasibility of carrying out a cost-effectiveness analysis in a full trial. Qualitative data from participants, volunteers, staff and carers will identify barriers and facilitators of a future full trial.

**Ethics and dissemination:**

The study has been approved by the London City and East Research Ethics Committee (reference 18/LO/2188). The findings will be presented at conferences and published in a peer-reviewed journal and in the National Institute of Health Research journals library. A public engagement seminar will be held at the end of the study aimed at key stakeholders.

**Trial registration number:**

ISRCTN63779614.

Strengths and limitations of the studyThis is the first pilot randomised controlled trial (RCT) of one-to-one befriending in people with intellectual disability.This pilot study will examine the feasibility and acceptability of carrying out a future RCT of befriending compared with an active control group.Community befriending services will be responsible for all aspects of the delivery of intervention.Availability of resources within befriending services may influence the delivery of the intervention.The findings will inform whether a full trial is feasible and what modifications would need to be made to overcome potential barriers.

## Introduction

Intellectual disability (ID) is a life-long condition characterised by impaired cognitive and adaptive functioning arising before the age of 18 years.^1^ The UK prevalence of ID is 1%–2%.^2^ People with ID have the same or higher prevalence of depression than the general population but are more likely to experience chronic depression.^3 4^ They have greater exposure to social disadvantage,^5^ experience social exclusion because of stigma,^6^ have markedly smaller social networks^7 8^ and a higher prevalence of loneliness compared with the general population.^9^ These factors have been associated with depressive symptoms in this group.^10–13^

### Conceptualisation of befriending

Befriending is ‘a relationship between two or more individuals, initiated, supported and monitored by an agency. The relationship is non-judgmental, mutual, purposeful, and there is a commitment over time’.^14^ Key attributes are that it is a one-to-one friendship-like relationship; it is an organised intervention; and there is a negotiation of power.^15^ There is a wide variation in the concept and practice of befriending.^16^ At one extreme, befriending is very close to a friendship, characterised as being reciprocal and is delivered by lay volunteers, and at the other end, it is a professional and therapeutic relationship, focused on the befriendee attaining goals and aspirations (mentoring). Most types of befriending relationships lie midway on this spectrum. Schemes are usually run by voluntary organisations in the community and offer training, supervision and ongoing support to volunteers.^16^

Befriending aims to help people who are lonely, isolated and have limited opportunities for social participation by increasing social and emotional support and by enhancing social networks and community participation. The causal mechanisms of befriending are unclear, but social support is thought to be important. Social support may act as a buffer to stress, and it may mediate genetic and environmental vulnerabilities to depression through its effects on neurobiological factors and other psychosocial factors (eg, coping strategies).^17^ The befriender may enhance social support and link the befriendee into social activities, which may be sustainable outside of and beyond the end of the befriending relationship, which may result in longer-term benefits. Befriending may also improve health outcomes through its effects on social networks.^18^

There are also potential benefits for befrienders. Motivation for befriending often includes a desire for ‘giving’ something back to the community (eg, helping others) and ‘getting’ something in return (eg, acquiring new skills or meeting new people).^19 20^ Positive benefits reported by befrienders include increased self-esteem and confidence, feeling that they have gained a genuine friend themselves and improved attitudes towards people with mental illness.^19^ Volunteering in general has beneficial effects on depression, psychological well-being and life satisfaction, and is associated with lower risk of mortality, although the causal mechanisms for these associations are unclear.^21^

However, the benefits of befriending may be short-lived, and people with ID have reported feeling distressed following the termination of their befriending relationship.^22^ Other risks include the emotional turbulence that is associated with a natural friendship, or harmful effects if the befriender is not adequately trained or supervised. There may also be undue burden placed on the befriender to take on excessive responsibility.^16^

### Effectiveness of befriending

One meta-analysis found that befriending in people with mental or physical health problems (delivered by social and healthcare professionals, as well as lay volunteers) had a statistically significant but modest effect on reducing symptoms of depression when compared with no treatment or treatment as usual in both the short and long term.^23^ Another systematic review examined a range of health and social outcomes in studies where befriending was delivered by volunteers only.^24^ Befriending was associated with better patient-reported outcomes when all primary outcomes were combined, but the effect size was small.^24^ However, in contrast to the previous review, there was limited evidence for the effectiveness of befriending on individual outcomes, such as depression, loneliness or quality of life, when the studies were combined.^24^ A recently published randomised controlled trial (RCT) of befriending by volunteers in people with psychosis provides further evidence for the potential beneficial effects of befriending.^25^ Participants in the intervention arm had significantly more social contacts at the end of the 12-month intervention and at 6 months’ follow-up, suggesting that befriending may help to reduce social isolation in this is group.

The effectiveness of befriending in people with ID has not been evaluated in a randomised trial. An unpublished single-arm feasibility study of one-to-one befriending by volunteers, conducted by a voluntary organisation,^26^ recruited 24 volunteers, of which 15 were matched with an individual with ID. Positive change was reported in 60% of individuals with ID; 53% reported a decrease in isolation, and 40% reported an increase in confidence. One Australian study examined the feasibility of using ‘active mentoring’, whereby members of existing community groups were trained to act as mentors to older adults with ID in order to provide social support and to encourage participation in community groups.^27^ The intervention comprised 29 individuals receiving the intervention and a matched comparison group. The participants in the intervention reported better social satisfaction compared with the comparison group, but there were no significant changes in the other outcomes.

Given the dearth of studies examining befriending in people with ID, there is a clear rationale for carrying out a pilot study prior to a full RCT.

## Aims and objectives

The main aim of the study was to determine the feasibility and acceptability of a full-scale RCT of one-to-one befriending by volunteers for people with ID in addition to usual care, compared with an active control arm.

The objectives were to

Examine the recruitment and retention of individuals with ID and volunteers in the trial and the number of successfully matched pairs within the 6-month study recruitment period.Record any negative consequences/adverse effects of befriending.Measure the extent to which the intervention is delivered as intended by volunteers and the befriending schemes.Examine the acceptability of the intervention and study procedures by exploring the views of individuals, volunteers, carers and befriending services.Examine changes in health and social outcomes by carrying out exploratory analyses of the impact of befriending on depressive symptoms measured by the Glasgow Depression Scale^28^ at 12 months and other outcomes (psychological distress, self-esteem, loneliness, quality of life and social participation) at 6 and 12 months postrandomisation.Carry out exploratory analyses of the impact of befriending on volunteers’ well-being, self-esteem, loneliness and attitudes towards people with ID at 6 and 12 months.Estimate the sample size required and determine the final trial design for a full-scale RCT.Assess the feasibility of collecting data that would inform a future analysis of cost effectiveness.

## Methods

### Design

This is a two-arm, parallel group, researcher blind pilot RCT with 1:1 allocation. Fifty participants with ID who are eligible for the study will be randomly allocated to either the intervention arm (one-to-one befriending by a volunteer) or an active control arm. Both groups will have access to usual care and a booklet of local resources. The duration of the intervention will be 6 months. Outcome assessments will be carried out at baseline, postintervention and at 6 months’ follow-up. A process evaluation, based on mixed methods, will be carried out to examine the delivery and adherence to intervention, and stakeholder views on the acceptability of the intervention and barriers and facilitators that may affect the implementation of a full-scale trial.

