### Sample size

We do not have any estimates of the number of people with ID who are eligible and are likely to consent to taking part in the trial. If we approach 50 participants who are eligible to take part, this will allow us to estimate an expected recruitment rate of 80% (40 people), with a 95% CI of 68.9% to 91.1%. A sample size of 40 recruited people with ID would allow us to estimate a 30% drop-out rate in the trial with a 95% CI of 25.7% to 54.3%. The recruitment period is 6 months. There are two participating befriending services and therefore we will need to recruit 3.3 participants with ID per month at each site. Twenty volunteers will need to be recruited and matched to each participant in the intervention arm.

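### The Design section says 50 participants will be randomised, but the abstract and the Sample size section plan for 40; the 50 is the number to be approached

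*Protocol article*

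**What the plan says.** The article states the size of the trial in three places.

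- **Design:** "Fifty participants with ID who are eligible for the study will be randomly allocated", in a two-arm trial with 1:1 allocation.
- **Abstract, Methods and analysis:** "The trial aims to recruit 40 participants with ID".
- **Sample size:** "If we approach 50 participants who are eligible to take part", the plan expects to estimate "an expected recruitment rate of 80% (40 people), with a 95% CI of 68.9% to 91.1"%. The retention calculation then starts from the smaller number: "A sample size of 40 recruited people with ID would allow us to estimate a 30% drop-out rate in the trial with a 95% CI".

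The Sample size section also gives two resource figures. On pace: "The recruitment period is 6 months", and "There are two participating befriending services and therefore we will need to recruit 3.3 participants with ID per month at each site". On volunteers: "Twenty volunteers will need to be recruited and matched to each participant in the intervention arm", which I read as one volunteer for each intervention participant.

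**The concern.** The number 50 has two roles. In the Sample size section it counts eligible people approached, before any of them has agreed to take part. In the Design section it counts people randomised. According to the Recruitment and Randomisation sections, an eligible person consents, completes the baseline assessment and is then randomised. The number randomised therefore cannot exceed the number recruited, and 50 randomised is incompatible with 40 recruited.

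The planned size is a figure that this pilot relies on. Recruitment is part of its first objective and is the first outcome listed. The size also sets the pace expected of two befriending services whose intervention costs, according to the Discussion, are not covered by the research funding. A reader who takes the size from the Design section will expect a trial 25% larger than the one that the rest of the article plans.

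**Working it through.** **Inputs.** From the Sample size section: 50 approached, 80% uptake, 40 recruited, 6 months, 2 sites, 3.3 recruits per site per month, 20 volunteers. From the Design section: 50 randomised, 1:1 allocation.

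**1. Recruitment-rate interval (the plan's own figure).** Wald interval: p ± 1.96 × √(p(1 − p)/n).

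- With p = 0.80 and n = 50: 1.96 × √(0.80 × 0.20/50) = 0.111, giving 68.9% to 91.1%. This is the printed interval.
- With n = 40 the same formula gives 67.6% to 92.4%, which is not.

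So 50 is the denominator of the uptake rate, that is, the number approached.

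**2. Monthly rate.** N/(6 months × 2 sites).

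- N = 40: 40/12 = 3.33, which matches 3.3.
- N = 50: 50/12 = 4.17, which does not.
- In reverse, 3.3 × 12 = 39.6. Allowing for rounding (3.25 to 3.35), N lies between 39.0 and 40.2.

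**3. Volunteers.** N/2, with one volunteer per intervention participant.

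- N = 40: 20, which matches.
- N = 50: 25, which does not.

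**4. What 50 randomised would require.** If only 50 are approached, uptake must be 50/50 = 100%, against the planned 80%. At 80% uptake, 50/0.80 = 62.5, so about 63 eligible people must be approached, and the recruitment-rate interval becomes about 70.1% to 89.9%.

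| Quantity | Printed | If 40 randomised | If 50 randomised |
|---|---|---|---|
| Per arm | not printed | 20 | 25 |
| Volunteers, one to one | 20 | 20 | 25 |
| Recruits per site per month | 3.3 | 3.33 | 4.17 |
| Approached at 80% uptake | 50 | 50 | about 63 |
| 95% CI for uptake | 68.9% to 91.1% | 68.9% to 91.1% | about 70.1% to 89.9% |

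**5. The drop-out interval.** The section prints 25.7% to 54.3% for a 30% rate. The Wald formula with p = 0.30 gives 15.8% to 44.2% at n = 40 and 17.3% to 42.7% at n = 50. The printed interval is centred on (25.7 + 54.3)/2 = 40%, and it equals the Wald interval for 40% with n = 45. Neither trial size explains it, so it is no evidence for either number.

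**The case against.** The strongest reply is that one descriptive sentence has picked up the wrong number, and that a careful reader can work out that 40 is meant. The trial is a pilot with exploratory estimation, and its size does not rest on power. Most of this stands. The abstract, the uptake interval, the monthly rate and the volunteer number agree with one another at 40, and only the Design sentence departs from them. It still needs correcting, because it states the size of the trial wrongly in the section where a reader would look for it.

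Four stronger readings are tempting, and the article does not support them.

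- *The planning figures contradict one another.* They do not. Those just listed agree at 40, and each conflicts only with the Design sentence.
- *Randomising 40 could be reported as either 100% or 80% of target, so the main feasibility result is open.* The sections on outcomes and analysis define recruitment as the share of eligible people who join. That denominator is observed, and no criterion shown is tied to a target count.
- *The number decides when recruitment stops.* The only limit stated is the 6-month period, in the Sample size section and the Study timeline.
- *Fifty randomised would require 25 volunteers.* The section on introducing and monitoring the relationship lets one volunteer serve several participants, so 20 could in principle cover an arm of 25. The volunteer number is therefore the weakest of the three checks. The monthly rate and the uptake calculation do not depend on it.

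**Conclusion.** The point holds as an unreconciled contradiction in the planned sample size: 50 randomised in the Design section, 40 recruited in the abstract and the Sample size section. The difference is 10 participants, or 25% of the smaller number. It carries through to 5 more per arm, 4.2 rather than 3.3 recruits per site per month, and about 63 rather than 50 people to approach.

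That 40 is the intended number is an inference. It is well supported, because the recruitment-rate interval and the monthly rate reproduce at 40 and not at 50, and the volunteer number fits 40 under one-to-one matching. That the Design sentence carried over the number approached is the likely explanation, but the article does not say so. An exact figure of 40 randomised also assumes no planned loss between consent and randomisation; none is described. The contradiction does not depend on that assumption. The consequence is limited to the stated size and the planning figures that follow from it.

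**What to change.** Reword the Design sentence to say that about 50 eligible people will be approached and that 40 are expected to be randomly allocated, 20 per arm. This is one sentence, and it changes nothing in conduct if 40 is the working number.

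If 50 randomised is really intended, leave the Design sentence and recalculate the abstract and the Sample size section: the target, the number approached, the uptake interval, the monthly rate, the retention denominator and, if matching is one to one, the volunteers.

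Correct the drop-out interval separately in either case. For a 30% rate the Wald interval is 15.8% to 44.2% with 40 participants.

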### Sample size

We do not have any estimates of the number of people with ID who are eligible and are likely to consent to taking part in the trial. If we approach 50 participants who are eligible to take part, this will allow us to estimate an expected recruitment rate of 80% (40 people), with a 95% CI of 68.9% to 91.1%. A sample size of 40 recruited people with ID would allow us to estimate a 30% drop-out rate in the trial with a 95% CI of 25.7% to 54.3%. The recruitment period is 6 months. There are two participating befriending services and therefore we will need to recruit 3.3 participants with ID per month at each site. Twenty volunteers will need to be recruited and matched to each participant in the intervention arm.

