### Outcomes

#### Recruitment and retention of participants

We will examine the proportion of participants with ID recruited from among those eligible, the proportion of volunteers recruited from among people expressing an interest over a 6-month period, the proportion of participants with ID who are successfully matched with a volunteer, the proportion of participants with ID and volunteers who drop out of the intervention arm and the proportion of participants and volunteers who complete subsequent follow-up assessments.

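### The 95% CI printed for a 30% drop-out rate with 40 participants (25.7% to 54.3%) is wrong: it is centred on 40%, and by the article's own method it should be 15.8% to 44.2%

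*Protocol article*

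**What the plan says.** The Sample size section gives no power calculation. It justifies the numbers by the precision of two feasibility proportions.

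- Recruitment: approaching 50 eligible people would allow the team to "estimate an expected recruitment rate of 80% (40 people), with a 95% CI of 68.9% to 91.1"%.
- Drop-out: the target of 40 is presented as a number that "would allow us to estimate a 30% drop-out rate in the trial with a 95% CI of 25.7% to 54.3"%.

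The Abstract also gives a recruitment target of 40. The Design section has a different number: "Fifty participants with ID who are eligible for the study will be randomly allocated".

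**The concern.** A Wald interval is symmetric about its estimate. The other common intervals for a proportion near 30% with 40 observations are only mildly asymmetric. In the printed interval, the 30% estimate lies 4.3 points above the lower limit (30 − 25.7) and 24.3 points below the upper limit (54.3 − 30). Such an imbalance does not arise from 12 drop-outs among 40.

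Retention is part of the pilot's first objective, and its precision is one of only two statistical arguments offered for the sample size. A reader who trusts the printed limits would conclude that an observed 30% drop-out rules out true rates below about 26% and leaves a loss of more than half plausible. For 40 participants neither conclusion holds. It is also unclear whether the rate or the interval is the mistake, so the planning assumption itself could be 30% or 40%.

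**Working it through.** **Inputs** (all from Sample size unless noted): 50 approached; 80% expected recruitment; 40 recruited; 30% drop-out, that is 12 of 40; 95% confidence; printed drop-out interval 25.7% to 54.3%. Alternative denominator: 50 randomised (Design).

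**Step 1. Identify the method from the interval that is right.** Wald: p ± 1.96·√(p(1−p)/n).

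0.80 ± 1.96·√(0.80·0.20/50) = 0.80 ± 0.111 = 68.9% to 91.1%.

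This is the printed recruitment interval. Wilson (67.0% to 88.8%) and exact (66.3% to 90.0%) do not reproduce it, so Wald is the article's method.

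**Step 2. Apply it to drop-out.**

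0.30 ± 1.96·√(0.30·0.70/40) = 0.30 ± 0.142 = 15.8% to 44.2%.

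The printed limits are too high by 25.7 − 15.8 = 9.9 points and 54.3 − 44.2 = 10.1 points.

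**Step 3. Try other methods for 12 of 40.**

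| Method | 95% CI |
|---|---|
| Wald | 15.80% to 44.20% |
| Wald, continuity corrected | 14.55% to 45.45% |
| Wilson | 18.07% to 45.43% |
| Agresti-Coull | 17.97% to 45.53% |
| Exact (Clopper-Pearson) | 16.56% to 46.53% |
| Jeffreys | 17.56% to 45.22% |

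No lower limit exceeds 18.1% and no upper limit exceeds 46.5%.

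**Step 4. Try other denominators at 30%.**

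- n = 50: 0.30 ± 1.96·√(0.21/50) = 17.3% to 42.7%.
- n = 20 (one arm): 0.30 ± 1.96·√(0.21/20) = 9.9% to 50.1%; exact 11.9% to 54.3%.

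Neither gives both printed limits. The exact upper limit for 20 agrees by chance, but its lower limit does not.

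**Step 5. See what the printed limits do fit.** Midpoint (25.7 + 54.3)/2 = 40.0%; half-width (54.3 − 25.7)/2 = 14.3 points.

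- 40% of 45, Wald: 0.40 ± 1.96·√(0.40·0.60/45) = 25.69% to 54.31%. This matches.
- 40% of 40, Wald: 0.40 ± 1.96·√(0.40·0.60/40) = 24.8% to 55.2%. No match.
- A search over n = 15 to 60, all counts and five methods found one other match to one decimal: Wilson for 16 of 41 (25.66% to 54.27%).

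**Step 6. Compare widths.** Half-width printed 14.3 points; correct for 30% of 40, 14.2 points. At 30%, a half-width of 14.3 points corresponds to n = 1.96²·0.21/0.143² ≈ 39.4.

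**The case against.** The best defence is that the slip has little consequence. The half-width hardly changes, the article ties no drop-out threshold to these limits, and the target, allocation, outcomes and analysis are unaffected. That stands, and it limits the weight of the point. It does not make the printed interval correct. No other statement in the article corrects it, and damage to the text is an unlikely cause, because the two limits together fit one coherent calculation.

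Three stronger readings are tempting, and the document does not support them.

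- *A reader might infer that 40 participants do not give the precision claimed.* Precision is the width, and 40 participants give 14.2 points against 14.3 printed. The limits are misplaced; the sample size is not undermined.
- *A reader might infer that the calculation was done for 45 participants.* The match needs a 40% rate as well as a denominator of 45, and the article attaches neither to drop-out. A second combination (Wilson, 16 of 41) also fits to one decimal. A leftover from another scenario is plausible, but the document does not show it.
- *A reader might infer that the denominator should be 20,* because one listed outcome is "the proportion of participants with ID and volunteers who drop out of the intervention arm". But the sample-size sentence concerns drop-out in the trial as a whole. The same outcome list includes completion of follow-up assessments, and the Analysis section reports drop-out from both arms. Intervention-arm drop-out is a separate outcome, and a condensed article need not give planned precision for each one.

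**Conclusion.** The drop-out interval is wrong as written. With 30% and 40 participants, the article's own method gives 15.8% to 44.2%, so both printed limits are about 10 points too high. True rates between about 16% and 26%, which the printed interval excludes, remain compatible with an observed 30%. Rates above about 44% (Wald) or 47% (exact), which it admits up to 54.3%, do not.

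This rests on two assumptions: that 30% is the intended rate and that 40 is the intended denominator. The rate cannot be confirmed from the article, since the interval points to 40%. The denominator of 40 has the Abstract and Sample size sections behind it, and the stated recruitment pace agrees (3.3 per month × 2 sites × 6 months = 39.6). The Design section's fifty does not. Under any of these readings (30% of 40, 30% of 50 or 40% of 40), the printed limits need changing.

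**What to change.** 1. In Sample size, replace the interval with 15.8% to 44.2%, which matches the method of the recruitment interval. If an exact interval is preferred, use 16.6% to 46.5% and name the method.
2. If 40% drop-out was the intended assumption, change the rate instead: 40% of 40 gives 24.8% to 55.2%.
3. Reconcile the fifty randomised in Design with the 40 in the Abstract and Sample size. If 50 is the true number randomised, the Wald interval for 30% becomes 17.3% to 42.7%.

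The cost is one corrected sentence and one reconciled number. No extra participants and no separate interval for the intervention arm are required.
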